## Abstract

**Background:**

Inclusive learning environments are considered as crucial for children’s engagement with learning and participation in school. Partnering for change (P4C) is a collaborative school-based service delivery model where services are provided at three levels of intensity based on children’s needs (class, group-, individual interventions). Interventions in P4C are provided universally to support all children with learning, not only children with special education needs (SEN), and as such are expected to be health-promoting.

**Aim:**

The aim of the study is to evaluate the effectiveness and cost-effectiveness of P4C as well as school staff members’ and children’s experiences after P4C.

**Methods:**

In a parallel, non-randomised controlled intervention design, 400 children, aged 6–12 years, and their teachers, will be recruited to either intervention classes, working according to the P4C, or to control classes (allocation ratio 1:1). Data will be collected at baseline, post-intervention (4 months), and 11 months follow-up post baseline. The primary outcome is children’s engagement with learning in school. Secondary outcomes include for example children’s health-related quality of life and wellbeing, occupational performance in school, attendance, and special educational needs. The difference-in-differences method using regression modelling will be applied to evaluate any potential changes following P4C. Focus group interviews focusing on children, and professionals’ experiences will be performed after P4C. A health economic evaluation of P4C will be performed, both in the short term (post intervention) and the long term (11-month follow-up). This study will provide knowledge about the effectiveness of P4C on children’s engagement with learning, mental health, and wellbeing, when creating inclusive learning environments using a combination of class-, group- and individual-level interventions.

**Trial registration number:**

NCT05435937.

**Supplementary Information:**

The online version contains supplementary material available at 10.1186/s12889-023-17053-0.

## Introduction

Participation in school is considered important for both learning and development, as well as for health and well-being to ensure that children reach their full potential across their lifespan [1]. It is widely recognised that engagement is related to participation and children’s learning across academic, social–emotional, and behavioural domains [2–5]. Children with poor engagement in school are more likely to experience difficulties with schoolwork, have fewer positive relationships with teachers, higher rates of bullying behaviour, risky health behaviours, and mental health problems [2]. Reports show that the proportion of school-aged children experiencing mental health problems is increasing [6], and is more common among children with disabilities [7, 8]. There is a clear link between mental health problems and restricted participation in school [9, 10]. For example, children with disabilities such as neurodevelopmental disorders (e.g., attention-deficit hyperactivity disorder (ADHD), autism spectrum disorder, conduct disorder) often report lower engagement with learning than their peers, and difficulties meeting educational requirements [11]. All these problems entail high costs for individuals, families, and for society at large [12]. Non-inclusive learning environments are considered to restrict children’s engagement with learning in school leading to difficulties meeting educational goals [13–17]. Thus, it is pivotal for schools to create inclusive learning environments to enhance engagement and participation. Identifying and providing interventions for children at risk of poor engagement with learning and restricted participation may have a beneficial effect on children’s mental health and well-being [11, 18, 19].

Partnering for change (P4C) is an innovative service delivery model aiming to enhance inclusive learning environments by providing a combination of class-, group- and individual-level interventions. Our hypothesis, supported by international research [20–22], is that implementing P4C will promote engagement with learning and well-being for all children, as well as help prevent mental health problems. P4C aims to create inclusive environments through capacity building, partnerships, and interdisciplinary collaboration in multiprofessional teams at schools [22]. Interventions according to P4C are built on universal design for learning (UDL) and are delivered according to a tiered approach on class-, group- and individual-levels. Hence, interventions focus both on school-wide interventions aiming to improve the learning environment for all children [23], as well as targeted intervention for children demonstrating low engagement with learning and participation restrictions in school [24–26]. Previous studies have shown promising results in P4C to accurately identify children in need of support [21, 27], positively influencing family–therapist relationships [28], increasing knowledge and capacity among teachers, parents, and occupational therapists (OTs) to identify and tailor support based on children’s needs [22, 29]. Additionally, P4C has proven to be effective in providing class-level interventions targeting the entire educational setting, which is important for health promotion [20]. However, there is limited research on P4C’s effectiveness on children’s engagement across social–emotional and behavioural domains. Additionally, the evidence on the cost-effectiveness of P4C is lacking. While P4C has been implemented and evaluated in Canada with promising results [21, 22, 27, 29], the service delivery model has yet to be implemented in Sweden. A previous study on the feasibility of P4C shows promising results concerning its implementation and acceptability ([name] et al., in manuscript). To promote implementation in Sweden, additional results are needed on the effectiveness of P4C on children’s engagement with learning, well-being, and occupational performance in school and its cost-effectiveness.

### Aim

The aim of the study is to evaluate the effectiveness and cost-effectiveness of P4C as well as school staff members’ and children’s experiences after P4C. The study addresses the following research questions:

What is the effectiveness of P4C on children’s: (a) engagement with learning, (b) health-related quality of life and well-being, (c) occupational performance, (d) attainment of school-based occupational performance goals, and (e) school attendance, (f) student–environment fit, and (g) number of children with special educational needs?Is P4C a cost-effective intervention compared to the control condition?How does P4C affect the school staff’s knowledge, skills, and experiences of P4C and children’s diverse needs?How do children in intervention classes experience their learning environment?

## Methods: participants, interventions, and outcomes

### Study design

The study will be conducted as a parallel, non-randomised controlled intervention study, with pre-, post- and 11-month follow-ups. It will include a qualitative evaluation involving interviews with school staff and children after P4C. The study will be conducted in elementary schools in Sweden during one school semester (approximately four months). In Swedish elementary schools, all pupils have access to Pupil Health Teams (PHTs), which will constitute treatment as usual (TAU). Intervention classes will also work according to P4C. Study design and enrolment details are presented in Fig. 1. This protocol is reported in accordance with the Standard Protocol Items: Recommendations for Interventional Trials (SPIRIT) [30] (Supplemental files 1). The intervention study has been approved by the Swedish Ethical Review Authority (2023-00013-02, 2021-06412-02, 2019-03954), and registered as a clinical trial at ClinicalTrials.gov (NCT05435937).

**Fig. 1 Fig1:**
[figure not shown]
Time schedule of enrolment, interventions and assessments. P4C, Partnering for Change; OT, Occupational therapist, TAU Treatment as usual

### Study setting and eligibility criteria

The intervention study will be conducted in elementary schools that include classes from preschool to sixth grade. Inclusion criteria for intervention- and control classes are: (a) preschool class or primary school class (grades 1–6), (b) have a Pupil Health Team with special education competence, (c) there are children with unmet special educational needs as perceived by the school staff, and (d) the principal and class teacher both consent to participate in the intervention study. The intervention classes will have access to an OT working according to P4C. OTs working according to P4C must have attended an online training course. Approximately 400 children in total (intervention and control, allocation ratio 1:1) will participate in the study.

### Recruitment

Information about OTs working in Pupil Health Teams in Swedish elementary schools will be retrieved using publicly available information on municipal websites and a closed Facebook group for OTs. Identified OTs will be provided with information about the intervention study, including study aims, the online training course in P4C, and the data collection methods—either via personal e-mail from the authors or via posts in the Facebook group. Principals, teachers, and/or special education teachers will be provided with information about the study by the OTs. Control classes will be recruited separately by contacting teachers and principals in different geographical areas. The control classes will be matched to the intervention classes based on class grade, gender, and socio-geographical area.

### Intervention classes receiving P4C

P4C is based on close collaboration, partnership, and knowledge translation (capacity building) between teachers and OTs, and is intended to create a sustainable inclusive learning environment that enhance children’s engagement with learning and participation [21, 22]. P4C is delivered based on the three-tiered approach, in which class-level interventions based on UDL, targeting the whole class, are implemented first, after which follow group-level interventions. Finally, when interventions in the first and second tier are not enough to engage all children in schoolwork, individual-level interventions are provided.

 Before applying P4C, participating OTs will attend an online training course consisting of seven digital modules, originally developed by the CanChild research group [22]. The modules were partly adapted to the Swedish school system. Furthermore, ongoing mentorship among participating OTs via web-based meetings will be arranged. For further details about P4C, please see Table 1.

**Table 1 Tab1:** Intervention-P4C

NAME	Partnering for Change in Sweden (P4C-Swe)
WHY	Capacity building through collaboration and coaching is essential for creating an inclusive learning environment. The core activities that make up this approach include relationship building, knowledge translation, and the three-tiered intervention approach.
WHAT *Materials* *Procedures*	Online training course for OTs *(Missiuna et al, 2012).* ‐ Includes seven modules (M1-M7) online (requires a license, available at: https://canchild.ca/en/partnering-for-change-ot-module ) ‐ Modules content: The P4C model, Universal Design for Learning, Consultative Collaboration; Dynamic Performance Analysis (DPA); Interventions using the three-tiered approach; Promoting sustainable change through knowledge translation, The school system - Each module includes readings, short videos, and learning tasks. - Access is provided to videos created by the research group specifically tailored to the Swedish context. This access also includes learning objectives and activities presented in Swedish, as well as references to websites and texts, such as a description of the Swedish school system. *1. An online training course for Occupational Therapists (OTs):* commences with a startup online discussion meeting. During this meeting, the research group introduces the P4C model and the course tailored for OTs applying the P4C approach. Subsequently, OTs individually study the seven modules (M1-M7) online. Throughout the online course, web-based discussion meetings are conducted and moderated by the research group to enhance the learning experience. Each of these forums lasts for two hours. *2. Delivering P4C (during a semester, approximately 4 months):* P4C is carried out by a multiprofessional team consisting of OT, teachers, and special education teachers in tier 1-3. Tier 1. Class level (Universal design for learning, UDL): The OT observes the class using DPA to identify children at risk of experiencing difficulties with occupational performance in school-based occupations (performance breakdown). Subsequently, the OT and teachers jointly discuss and analyze the causes of non-performance, establish goals and implement adjustments/interventions at the UDL level to enhance occupational performance. The teacher implements the agreed upon interventions, followed by further observations by the OT to evaluate the outcome. If, after implemented UDL interventions, there are still children with difficulties in carrying out current school-based occupations, P4C will proceed to Tier 2. Tier 2. Group level (Differentiated instruction): If, after implementing UDL interventions, there are still children experiencing performance breakdowns, the OT conducts new observations based on DPA. Working in collaboration with teachers, the OT then implements interventions for a group of children, followed by subsequent observations by the OT. Tier 3. Individual level (Accommodations): After Tier 1 and 2, if children continue to experience performance breakdowns, the OT collaborates with the teachers to identify and implement individual-level interventions. *3. Web meetings:* Occur once a month and involve OTs, teachers, and special education teachers collaborating with the research group to monitor and support the implementation of P4C.
WHO PROVIDE	The OT, a part of the schools' Pupil Health Team, collaborates with teachers to implement adjustments and support using the P4C.
HOW AND WHERE	Observations: take place in natural settings in schools. Collaboration: occurs both on school premises and via web meetings.

During the intervention period, the OT will collaborate closely with teachers in intervention classes. The OT will be present in the classroom (about 1/2 day a week). The Dynamic Performance Analysis (DPA) [31] will be used to identify children experiencing difficulties with occupational performance in school (performance break downs). The OT and teacher will jointly analyse the observed difficulties, formulate school-based occupational performance goals, and in collaboration, decide and follow up on interventions needed to prevent or overcome low engagement with learning in school.

### Control classes

According to the Educational Act [32], schools are obliged to identify needs and provide and evaluate extra adaptations (e.g., cognitive support, adapted instructions) in regular classrooms. If the adaptations are not enough, a child may be provided special support including regular contact with a special education teacher, pupil’s assistant, and/or placement in a special teaching group. Children in control classes will receive TAU provided by the Pupil Health Team, which most often consists of adaptions/support provided by a school doctor, school nurse, or psychologist, as well as staff with special educational competence.

### School and public involvement

#### Reference group

A reference group, comprised of representatives from organisations at different levels of government in Sweden, such as the Swedish Association of Local Authorities and Regions, and the National Agency for Special Needs Education and interest organisations will be constituted. The reference group will be involved in discussions concerning methodological issues, interpretation, and disseminating the results. The reference group will meet on a regular basis throughout the study period.

### Outcome measures

Data collection will occur at: (i) baseline, prior to the intervention (T1); (ii) immediately following the intervention (T2); and (iii) eleven months follow-up post-baseline (T3). An overview of all outcome measures and data collection points is presented in Table 2.

**Table 2 Tab2:**
[figure not shown]
Overview of the study period, interventions, and data collection points

* T0 = Before training course in P4C; T1 = Before intervention, T2 = After intervention; T3 = Follow-up

** Engagement Versus Disaffection With Learning: Teacher Report (EEL); Swedish Child Health Utility 9D (CHU9D); How I Feel About My School (HIFAMS); School setting interview (SIS)

#### Effectiveness and cost-effectiveness of P4C

The primary outcome is children’s *engagement with learning*, measured by ‘Engagement Versus Disaffection with Learning: Teacher Report’ (EEL), focusing on children’s engagement and disaffection with learning in school [33]. The EEL consists of four subscales across 25 items, rated on a four-point Likert scale, ranging from 1 (happens almost never) to 4 (happens very often), and is rated by teachers. The subscale behavioural engagement (5 items) focuses on effort, attention, and persistence in initiating and participating in learning activities. The sub-scale of behavioural disaffection (5 items) addresses a lack of effort and withdrawal from learning. The third sub-scale—emotional engagement (5 items) —focuses on emotions indicating motivated involvement during learning activities; and emotional disaffection (9 items) addresses emotions indicating withdrawal during learning. The EEL has been shown to have good convergent validity and good test–retest reliability, and to differentiate between behavioural and emotional school engagement [4, 34]. Timeframe: baseline, four months, eleven months (both intervention and control classes).

Secondary outcomes include data on *children’s health-related quality of life (HRQOL) and wellbeing*, *children’s occupational performance*, *attainment of school-based occupational performance goals*, *school attendance, and student-environment fit*. Also, *teacher and OT knowledge and skills*, as well as *documentation of services provided* including *data on special educational needs* will be collected. Additionally, focus group interviews will be performed with school staff and children after P4C.

Children’s *HRQOL* will be measured using Swedish Child Health Utility 9D (CHU9D), a generic preference-based HRQOL measure constructed for use in children and youth. CHU9D has nine questions representing nine dimensions of HRQOL: worried, sad, pain, tired, annoyed, schoolwork/homework, sleep, daily routine, and activities [35]. Each question has five response levels representing increasing degrees of severity within each dimension and is self-completed by the child. The CHU9D has shown to be practical to use, and has acceptable face and convergent validity and internal consistency [36–39]. The CHU9D has been validated in a Swedish context and has been shown to be a feasible, reliable, and valid measures of preference based HRQOL [40]. Timeframe: baseline, four months, eleven months (both intervention and control classes).

Children’s *well-being* in school-related situations will be measured using How I Feel About My School (HIFAMS) [41]. HIFAMS addresses well-being in seven school-related situations: on the way to school, in the classroom, when doing work, at the playground, thinking about other children, thinking about their teacher, and about school in general. The HIFAMS uses a three-point Likert scale, where emotions are used to convey the responses sad (0), OK (1), and happy (2), and is self-completed by the child. The total score is calculated as the sum of the individual items (maximum total score:14), with higher scores indicating greater happiness. HIFAMS is suitable for children aged 4 to 12 years. It has shown moderate internal consistency and test–retest reliability [41, 42]. In a Swedish sample, the HIFAMS showed moderate and satisfactory internal consistency [42]. Timeframe: baseline, four months, eleven months (for both intervention and control classes).

*Occupational performance* in school-based activities will be observed by OTs and documented in a digital questionnaire created especially for the study and distributed using Survey&Report. The digital questionnaire is based on the Dynamic Performance Analysis (DPA) [31] and uses a rating scale (1–10), being 1 = no performance 10 = excellent performance. *Attainment of occupational performance goals* will be rated as attained, partly attained, or not attained before and after implemented interventions for each identified performance breakdown using the digital questionnaire. Time frame: continuously during the four-month intervention period (intervention classes).

*School attendance* per week (%) will be retrieved from the schools’ registration on children’s attendance. Time frame: baseline, four months, eleven months (for both intervention and control classes).

*Student-environment fit* in school setting will be examined only before and after individual-level interventions using the School Setting Interview (SSI) [43]. The SSI includes 16 items concerning everyday school activities, and the children’s perceived need for adjustments before and after implemented interventions. Each item is scored using a four-step rating scale; 4 = perfect fit, 3 = good fit, 2 ≤ partial fit, and 1 = unfit. The SSI has shown usability and construct validity [44]. Time frame: applied continuously during the four-month intervention period (intervention classes).

Data on the number of children who have *access to adaptions and/or special support* will be registered by teachers in each class, as will the number of children in need of additional adaptions and support. Time Frame: baseline, four months, eleven months (for both intervention and control classes).

All delivered interventions will be documented by OTs and teachers in a digital questionnaire created and distributed using Survey&Report. The type and level of interventions (class, group, individual), as well as time needed to deliver P4C each week will be documented. The questionnaire is developed for the project and has been previously used by OTs and teachers in Swedish schools. Time frame: weekly during the four-month intervention period (intervention classes).

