### Statistical analysis

#### Effectiveness of P4C

Descriptive statistics will be presented for demographic characteristics and outcome variables. To evaluate any potential changes following the P4C, the difference-in-differences method using regression modelling will be applied [45]. This method compares the changes in outcomes over time between the intervention and control group and allows for adjustment for confounders. Furthermore, the multilevel structure of the design of the study will be considered. If the proportion of missing data is between 5% and 40%, multiple imputation will be performed [46]. Estimates will be reported with 95% confidence intervals and associated p-values. A two-tailed p-value of < 0.05 will be considered statistically significant.

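### Three of the seven outcomes in the effectiveness question are collected only in intervention classes, so the planned difference-in-differences cannot be estimated for them

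*Protocol article*

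**What the plan says.** In the protocol article, section Aim, the first research question opens with "What is the effectiveness of P4C on children’s" and then lists seven lettered items. Items (a) and (b) are engagement, and quality of life with well-being. The list goes on with "c) occupational performance, (d) attainment of school-based occupational performance goals, and (e) school attendance, (f) student–environment fit, and (g) number of children" with special educational needs.

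The section Effectiveness and cost-effectiveness of P4C, under Outcome measures, names occupational performance, goal attainment and student-environment fit as secondary outcomes, alongside outcomes that are measured in both arms. It does not mark them as descriptive or as process measures. It collects them as follows:

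- Occupational performance (c) "will be observed by OTs and documented in a digital questionnaire created especially for the study". Goal attainment (d) is rated "before and after implemented interventions for each identified performance breakdown using the digital questionnaire". One time frame covers both: "Time frame: continuously during the four-month intervention period (intervention classes".
- Student-environment fit (f) "will be examined only before and after individual-level interventions using the School Setting Interview (SSI", again in intervention classes and during the intervention period.

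Under Statistical analysis, Effectiveness of P4C, the method is difference-in-differences by regression. The article explains: "This method compares the changes in outcomes over time between the intervention and control group". Apart from descriptive statistics, no other effectiveness analysis is named.

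**The concern.** The question, the data collection and the method do not fit together for (c), (d) and (f). The question is causal, the data come from one arm, and the method needs two.

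If the study reports a before-after change for these outcomes in answer to research question 1, readers will see it next to controlled results and may give it the same weight. A one-arm change over a school semester mixes any P4C effect with the children's ordinary development and with the usual Pupil Health Team support, which intervention classes also receive (Study design). With no control change to subtract, these parts cannot be told apart.

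**Working it through.** No figure in the plan bears on this point. The check is a count of outcomes by arm, followed by a look at what the named method can estimate.

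**Step 1. Outcomes by arm** (research question 1 in Aim, set against the time frames under Outcome measures)

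| Item | Measure | Classes | Timing in the text |
|---|---|---|---|
| (a) engagement | EEL, teacher-rated | both | baseline, 4 and 11 months |
| (b) quality of life, well-being | CHU9D, HIFAMS, child-rated | both | baseline, 4 and 11 months |
| (c) occupational performance | 1–10 rating by OTs | intervention only | during the 4-month period |
| (d) goal attainment | three categories, per identified breakdown | intervention only | during the 4-month period |
| (e) attendance | school registration | both | baseline, 4 and 11 months |
| (f) student-environment fit | SSI | intervention only | around individual-level interventions |
| (g) special educational needs | teacher counts of access to and need for support | both | baseline, 4 and 11 months |

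Four outcomes (a, b, e, g) are measured in both arms and three (c, d, f) in one arm: 4 + 3 = 7.

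**Step 2. What difference-in-differences needs**

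The estimate is (intervention after − intervention before) − (control after − control before). For (c), (d) and (f) the second bracket has no observations.

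In regression form, outcome = b0 + b1·group + b2·time + b3·group×time, and b3 is the effect. If every record has group = 1, group cannot be distinguished from the intercept, and group×time cannot be distinguished from time. Only the sum b2 + b3 can be estimated. Reading that sum as the effect requires b2 = 0, that is, no change over the semester without P4C. Neither more children nor adjustment for confounders removes this requirement.

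**Step 3. What else could sit in a one-arm change, outcome by outcome**

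- (d) is rated for each identified performance breakdown, so measurement starts where a difficulty has been found.
- (f) is measured only around individual-level interventions. Table 1 gives these to children whose breakdowns persist after Tiers 1 and 2. Entry at a low point is therefore explicit here too.
- (c) carries no such limit in its own sentence. Table 1 has the OT observe the class with the Dynamic Performance Analysis, and Intervention classes receiving P4C says this tool is used to find children in difficulty. Selection for (c) is an inference from these two places. What is explicit for (c) is the rater: the OTs, who also help to plan and deliver P4C.

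**The case against.** The strongest reply is that this is only a matter of labels. The article openly marks the three measures as belonging to intervention classes. It never says that they enter the difference-in-differences model, and it also plans descriptive statistics for outcome variables. How one-arm secondary measures are summarised is commonly left to an analysis plan, which is not shown, and the content of Table 2 is not shown either. Goal attainment can exist only where P4C goals are set, so its lack of a control is inherent.

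Much of this stands, and it limits the point. All three outcomes are secondary, and the article does not commit to comparative p-values for them. It does not remove the mismatch. The article itself puts these outcomes in the effectiveness question and fixes their collection to one arm. An analysis plan could add a within-group summary but could not supply control observations.

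A reader might infer more than the documents support:

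- **That all three outcomes are measured only in children selected for poor performance.** This is stated for (d) and (f) only.
- **That all three are rated by the people delivering P4C.** The OT is named as rater for (c) only. No rater is named for (d), and the SSI concerns needs as the child perceives them.
- **That regression to the mean can be put in SD units and set against the EEL difference the trial is sized for.** The documents give neither the reliability of these measures nor the depth of selection. An SD-unit formula does not fit a three-category goal rating. It does not carry over to the SSI either, because children reach that measure through OT observation and not through a low SSI score. The EEL difference is a between-group figure on another instrument.

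**Conclusion.** The point holds as an inconsistency in the protocol article. For three of the seven outcomes in research question 1, the named effectiveness method cannot be estimated, and a before-after change cannot answer the question as worded. This rests only on the stated time frames and the stated method, and needs no outside assumption.

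The direction and amount of any bias in a one-arm change cannot be derived from the documents, so none is given. Entry at a low point is a possible contributor for (d) and (f), and rating by those who help deliver P4C is one for (c). The primary outcome and the other outcomes measured in both arms are untouched. The change should be made, but it does not threaten the trial's main conclusion.

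**What to change.** 1. Take (c), (d) and (f) out of research question 1 and put them in a separate question on what happens within intervention classes.
2. Label them descriptive within-intervention (process) outcomes, reported without effectiveness claims or effectiveness p-values.
3. In Statistical analysis, state that difference-in-differences applies only to outcomes measured in both arms. For the children these are EEL, CHU9D, HIFAMS, attendance, and access to or need for support.

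The cost is wording in the aim, the outcome list and the analysis section, and the loss of three secondary effectiveness claims. No new data are needed. Under Ethics and dissemination the article already undertakes to report important changes of outcome to the registry; whether the registry entry needs changing cannot be seen from the documents.

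The alternative is to collect (c), and if feasible (f), in control classes on a comparable group of children defined in advance. That would keep the effectiveness question for those outcomes, but it needs observers and assessments that the article does not plan. It would not help (d), whose goals exist only where P4C sets them.
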